#### Randomization

Participants will be randomly allocated to the control group or one of two ESM intervention groups (“Do-module” and “Think-module”). Randomization (allocation ratio 1:1:1) will be stratified per treatment location according to the duration of antidepressant pharmacotherapy (new/switch vs. maintenance, i.e., receiving antidepressant or mood stabilizing medication for less vs. longer than 8 weeks prior to study entry), and current psychotherapy (yes or no). For these different strata, separate blocks with an allocation sequence of six with an equal condition distribution will be created using an online randomization tool (https://www.random.org/lists). Thus, each of the three conditions will be present twice in a block of six. The allocation will be implemented by using sequentially numbered sealed envelopes (i.e., one pile of envelopes for each stratum). The allocation will be done during the introduction session, by team members who do not have access to the allocation sequence. Participants and research assistants are obviously not blind to treatment. Practitioners are not blind to treatment per se; participants decide themselves whether they want to discuss their feedback reports with their (future) therapist.

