### Participants

We will recruit 150 male and female adult patients referred for depressive complaints to general or specialized outpatient teams at mental health care organizations in the North of the Netherlands. Participants will be recruited within the research network of mental health institutions in the North of The Netherlands, the Rob Giel Research Center (https://www.rgoc.nl), which covers a catchment area of over 4 million inhabitants. Eligibility criteria are broad to include typical patients. Inclusion criteria are: a) indication for depression treatment by the mental health care professional (hereafter named: practitioner); b) age between 18 and 65 years; and c) written informed consent. Exclusion criteria are (based on practitioners’ appraisals): a) crisis intervention warranted (i.e., in the case of acute suicidality); b) presence of psychotic or manic symptoms; and c) incapability of following research procedures due to inadequate Dutch language proficiency, significant auditory or visual impairments or mental retardation. Patients will be enrolled in regular treatment upon availability, that is, the start of regular treatment will not be postponed until participation in ZELF-i finishes. The ZELF-i intervention is intended as an add-on tool at the start of care as usual and thus circumstances are otherwise kept as ‘natural’ as possible. Participants will receive travel reimbursements and an additional €10 if they used the data bundle of their own smartphone to participate in the intervention.

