### Statistical analyses

#### Efficacy of the ESM-modules

The data have a hierarchical structure, because multiple IDS-SR assessments will be clustered within participants. Therefore, multilevel regression analyses will be used with the two-way interaction between time (in weeks) and treatment allocation as fixed effects, participants as random intercept and a (linear or quadratic) random slope for time (similar to [15]). This way, we can examine the effect of time on depressive symptoms (across 6 IDS-SR measurements), the effect of group (3 levels: Do-module, Think-module, Control), and the interaction between time and group separately. Similar analyses will be performed to investigate the impact of the ESM-modules on empowerment (NEL) and functioning (OQ-45). In order to take into account individual differences regarding the time interval between the start date of the participation in ZELF-i and the start date of the treatment at the mental health organization, a covariate “start date treatment – start date ZELF-i” will be included in the analyses. Thresholds for statistical significance will be set at *p* < .05.

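### The efficacy model omits all three factors used to stratify randomisation, which costs a little precision if those factors predict change in IDS-SR

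*Protocol article*

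**What the plan says.** Under Randomization, allocation to the three arms is "stratified per treatment location according to the duration of antidepressant pharmacotherapy" and by whether the patient currently has psychotherapy. The two medication levels are described as "receiving antidepressant or mood stabilizing medication for less vs. longer than 8 weeks prior to study entry". Each stratum has its own blocks and its own pile of envelopes, and "each of the three conditions will be present twice in a block of six".

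Under Efficacy of the ESM-modules, "multilevel regression analyses will be used with the two-way interaction between time (in weeks) and treatment allocation as fixed effects", with "participants as random intercept and a (linear or quadratic) random slope for time". One covariate is named, the interval between the start of ZELF-i and the start of regular treatment. Location, medication duration and psychotherapy do not appear. The Discussion adds that differences between locations in the added value of the intervention will be explored.

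Under Participants, entry requires "indication for depression treatment by the mental health care professional", an age limit and consent. It does not require medication.

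**The concern.** Stratified blocks make the arms nearly equal on the stratification factors, so those factors contribute little to the chance difference between arms. A model that leaves them out still counts their variation as noise. The reported standard error is then larger than the true sampling variation of the comparison, and the test rejects less often than its nominal level. Recent medication changes and ongoing psychotherapy could plausibly affect how IDS-SR scores change, so some precision may be lost.

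This goes beyond a detail left to a later plan: the article lists the model's terms and chooses a covariate, and that list does not match the design described a few sections before it.

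A smaller, related point concerns the medication factor. Both levels are worded for people receiving medication, and the article does not say where a patient without medication is placed.

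**Working it through.** **No figure of the plan's own to reproduce on this point.** The article gives no prognostic strength for the strata and no SD for IDS-SR. Its stated 85–99% power (Sample size calculation) therefore cannot be rebuilt from the text and is not used below.

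**1. A simple difference in level between arms.** If balanced strata explain a share R² of the between-person variance (assumed), leaving them out inflates the reported standard error by 1/√(1−R²), and the actual two-sided level is 2[1−Φ(1.96/√(1−R²))].

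| R² (assumed) | SE inflation | Actual level of a 5% test |
|---|---|---|
| 5% | 1.03 | 4.4% |
| 10% | 1.05 | 3.9% |
| 20% | 1.12 | 2.8% |
| 30% | 1.20 | 1.9% |

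This is not the efficacy contrast. The plan tests time by arm, with a random intercept that already takes up stable differences between people.

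**2. The time-by-arm contrast, by simulation of the stated model.** Inputs from the article: 150 participants, three arms, six assessments, blocks of six. Assumed inputs: four locations, hence 4 × 2 × 2 = 16 strata; intercept SD 9.3 and residual SD 7.6, chosen so that 9.3²/(9.3² + 7.6²) = 86.5/144.3 = 0.60, the article's pre-post correlation; slope SD 3 points per 10 weeks; complete data; 300 runs per scenario.

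Mean reported SE of the time-by-arm coefficient:

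| Strata explain (intercept / slope variance) | No strata | Main effects only | Main effects and × time |
|---|---|---|---|
| 0% / 0% | 0.875 | 0.875 | 0.877 |
| 30% / 0% | 0.875 | 0.875 | 0.877 |
| 10% / 10% | 0.875 | 0.875 | 0.857 |
| 30% / 30% | 0.875 | 0.875 | 0.816 |

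- Main effects alone change nothing, even when the strata explain 30% of the intercept variance.
- Interactions with time reduce the SE by 1 − 0.857/0.875 = 2.1% and 1 − 0.816/0.875 = 6.7%.
- In variance terms this is 1 − 0.979² ≈ 4% and 1 − 0.933² ≈ 13%. Without adjustment, reaching the same reported SE would take about 150 × (0.875/0.857)² ≈ 156 or 150 × (0.875/0.816)² ≈ 172 participants.
- If the strata predict nothing, the extra terms cost 0.877/0.875 − 1 ≈ 0.2%.

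**3. Direction of the error.** In the 30% / 30% case the unadjusted reported SE (0.875) exceeds the observed spread of the estimates (0.832). The adjusted SE (0.816) matches its own spread (0.818). In the 10% / 10% case the unadjusted figures are 0.875 and 0.871, so the conservatism is barely visible. Rejection rates at 30% / 30% were 4.0% unadjusted and 5.3% adjusted. With 300 runs the Monte Carlo error is √(0.05 × 0.95/300) ≈ 1.3 percentage points, so these rates do not differ clearly. None of them indicates inflation.

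**4. Size of the model change.** With four locations, three-level medication and psychotherapy there are 3 + 2 + 1 = 6 main-effect parameters. Interactions with linear time make 12. With quadratic time it is 18.

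**The case against.** The strongest reply is that little is at stake. The plan tests a time-by-arm interaction with random intercept and slope, so strata that shift only the level of IDS-SR do no harm to it. A gain needs strata that predict the slope, and the article says nothing about that. Even then the gain is a few per cent, and the error is on the safe side. All of this stands, and it sets the weight of the point.

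A second reply is that adjustment for strata is often left to the analysis plan, and that naming one covariate for a specific reason does not exclude others. This has some force. The efficacy section does spell out its terms, however, so the mismatch is fair to raise. The exploration of locations in the Discussion does not close it: that concerns variation in the intervention's benefit between sites and does not put location in the efficacy model. Nor does that text predict prognostic site effects. It says only that practitioners' acceptance and integration could differ.

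A reader might infer that unmedicated patients have no stratum and that allocation is therefore compromised. The text does not support this. Zero duration can be read as less than 8 weeks, and allocation within any stratum remains random. What remains is a gap in wording. A third envelope level would raise the strata per location from four to six and thin the cells under blocks of six.

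**Conclusion.** The point holds with modest weight. The efficacy model omits all three stratification factors. If they predict change in IDS-SR, the time-by-arm standard error is too large by roughly 2% (strata explaining 10% of slope variance) to 7% (30%). Those shares, the number of locations, the SDs and complete data are assumptions; only the correlation of 0.6 and the design features come from the article. The error is conservative.

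A reader might go further and infer that a nominal 5% test really runs near 3%, or that intervals are markedly too wide. Those figures belong to a simple between-person comparison with strongly prognostic, perfectly balanced strata. They do not carry over to the interaction test, and the article supports no such strength. Nor does it support describing the trial as planned at about 80% power, since it states 85–99%.

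**What to change.** Prespecify in the efficacy model fixed effects for location, medication status and current psychotherapy, each with its interaction with time. Pool locations with few participants by a rule set in advance. Use the same terms for the NEL and OQ-45 analyses, which are planned along the same lines.

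In the model, medication can be coded none / up to 8 weeks / longer than 8 weeks from baseline data. State in the protocol which existing stratum unmedicated patients enter, and leave the randomisation levels and envelopes as they are. If that placement is consistent, the three-level coding refines the randomised strata.

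The cost is wording and model degrees of freedom: about a dozen parameters with four locations and linear time, and 18 if time is quadratic. No new data are needed, because location is known and medication use and psychotherapy are recorded at baseline.

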### Procedure

#### Recruitment

An overview of the study design is presented in Fig. 1. Individuals scheduled for intake at one of the participating mental health care teams will receive an information letter about ZELF-i and a contact consent form together with their intake invitation. Through the information letter, participants will be made aware of the procedure that, at the end of the intake, the practitioner will discuss the possibility to participate in ZELF-i with them if a) depression treatment is indicated, and b) the practitioner deems ZELF-i suited for the patient. Participants will be made aware that participation is voluntary and refusal to participate will not affect their treatment. Patients decide independently whether they are interested in the research and want to be contacted by the research team by sending back the consent form or bringing it to the intake at the mental health care institution. It is important that eligible participants are enrolled in the study shortly after the intake, because the intervention (28 days) is designed to support participants early on and bridge potential waiting periods between the intake and the start of the indicated depression treatment in a constructive way. Therefore, eligible participants will be contacted by a research assistant preferably within a few days after the intake to answer any questions and schedule an appointment for the introduction session of the intervention study.

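### A single fixed block size of six in an open-label trial, and a medication factor with no explicit place for unmedicated patients, make some allocations deducible and leave the choice of pile open

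*Protocol article*

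**What the plan says.** All of this is in the protocol article, mainly under Procedure, Randomization.

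- **Ratio and strata.** "Randomization (allocation ratio 1:1:1) will be stratified per treatment location according to the duration of antidepressant pharmacotherapy", and also by current psychotherapy (yes or no). That makes four strata per location. The number of locations is not given.
- **Medication levels.** "new/switch vs. maintenance, i.e., receiving antidepressant or mood stabilizing medication for less vs. longer than 8 weeks prior to study entry".
- **Blocks.** "separate blocks with an allocation sequence of six with an equal condition distribution will be created using an online randomization tool", and "Thus, each of the three conditions will be present twice in a block of six".
- **Concealment.** Sealed envelopes numbered in order, one pile per stratum, opened during the introduction session by staff without access to the list.
- **Blinding.** "Participants and research assistants are obviously not blind to treatment". Practitioners are not necessarily blind either.

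Other sections bear on the point:

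- **Recruitment.** The practitioner judges whether the study suits the patient. Then "eligible participants will be contacted by a research assistant preferably within a few days after the intake", to answer questions and make the appointment.
- **Introduction session and baseline measurement.** Written consent comes before allocation, and the questionnaires come last.
- **Participants.** Entry requires an indication for depression treatment, an age between 18 and 65 and consent. Being on medication is not required.
- **Other study parameters.** Medication use and current psychotherapy are recorded by a baseline questionnaire.

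**The concern.** Withholding the list protects it from being read, but not from being inferred. With one constant block size, a person who sees the arms already drawn from a pile can deduce the end of each block. Staff here are unblinded, and some of them have contact with patients before consent. Encouragement, or the timing of an appointment, could therefore depend on which arm is likely to come next.

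The medication factor raises a separate question. Both of its levels describe people who are receiving a drug. Patients are approached around intake, before or near the start of treatment, so unmedicated patients are eligible and may be common. If their pile is not fixed in advance, different staff may classify them differently, or a pile may be chosen at the draw. That choice comes after consent, so the consent safeguard does not cover it.

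The primary outcome, the IDS-SR, is self-reported, and the control group receives no additional intervention. If foresight influenced who entered which arm, the arms could differ in motivation or other unmeasured traits, and a model would not reliably correct for that.

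**Working it through.** **Inputs from the article:** three arms, 1:1:1, block of six; 2 × 2 = 4 strata per location; 150 participants (Sample size calculation, Group analyses). **Assumptions:** the number of locations L (range 1 to 10); participants spread evenly at random over the 4L strata; an observer who knows the block size and all earlier allocations in the pile.

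**Step 1. Block composition.** 6/3 = 2 per arm, which agrees with the article. The number of equally likely orders is 6!/(2!·2!·2!) = 90.

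**Step 2. Certainty within a complete block.** The 6th allocation is always known. The 5th is known only if the last two envelopes hold the same arm: 3 × 4!/(2!·2!) / 90 = 18/90 = 0.20. Positions 1 to 4 are never certain. The average is (0 + 0 + 0 + 0 + 0.20 + 1)/6 = **0.20**.

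**Step 3. Best guess within a complete block.** Enumerating the 90 orders gives a probability of a correct best guess at positions 1 to 6 of 0.333, 0.400, 0.500, 0.533, 0.600 and 1. The average is 3.367/6 = **0.561**, against 0.333 without foresight. Control is ruled out for 22.2% of allocations and certain for 6.7%.

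**Step 4. Incomplete blocks.** The mean stratum size is 150/(4L): 37.5 for L = 1, 7.5 for L = 5 and 3.75 for L = 10. Small strata often stop before a block closes, so fewer allocations are certain. The table gives simulated values. The observer facing mixed blocks of 3, 6 and 9 is assumed to know the set of sizes but not the current one, and to guess optimally.

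| Locations (assumed) | Certain, fixed 6 | Certain, mixed 3/6/9 | Best guess, fixed 6 | Best guess, mixed 3/6/9 |
|---|---|---|---|---|
| 1 | 18.7% | 3.4% | 55.1% | 54.5% |
| 3 | 16.1% | 2.5% | 53.4% | 52.9% |
| 5 | 13.8% | 1.4% | 51.7% | 51.1% |
| 10 | 6.5% | 0.1% | 46.6% | 46.9% |

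Mixing sizes nearly removes certainty but leaves best-guess accuracy about where it was.

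**Step 5. The medication factor against eligibility.** The levels are "receiving antidepressant or mood stabilizing medication for less vs. longer than 8 weeks prior to study entry". The Participants section admits patients on no medication. If the factor is read as a duration cut at 8 weeks, zero weeks falls on the shorter side. If it is read by its labels, someone who has neither started nor switched a drug matches neither. The first reading is the more natural one, but no sentence states it. The article also does not say how the stratum is known before the envelope is drawn: the questionnaire that records medication and psychotherapy is completed after allocation.

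**The case against.** The article describes real safeguards. The envelopes are sealed and numbered, consent comes first, and those who allocate have no list. The patient volunteers by returning a contact form, and at the draw nobody is described as having discretion over entry. These points stand, and they narrow the route for selection to contact and scheduling before consent and to the choice of pile.

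Four stronger readings are tempting but are not supported:

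- **That staff see every past allocation, or that the assistant who telephones knows the history of the pile.** The article says neither. It does not say that the scheduler and the allocator are the same person, or that the scheduler knows the patient's stratum when calling. Printing the block size in the article does not show that recruiters knew it.
- **That an assistant must choose between two piles for each unmedicated patient.** A duration cut at 8 weeks most naturally puts them in the shorter level, and the full protocol may hold a working rule. With free choice, perfect recall and complete blocks, the chance of obtaining a wanted arm would rise from 33% to 47%. That is a ceiling for an unknown share of patients, not an estimate.
- **That selection bias has occurred and would be beyond detection.** Nothing shows that it occurred. Baseline IDS-SR is collected, so steering on severity would at least be partly visible.
- **That varied blocks make allocation hard to guess.** They remove certainty, while best-guess accuracy hardly falls. Larger mixes such as 6, 9 and 12 lower it more (47.0% with 5 locations), but suit strata averaging 7.5 patients poorly.

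**Conclusion.** The point holds in a limited form. One constant block size in an open-label trial with a pile per stratum makes up to 20% of allocations deducible, or between 18.7% and 6.5% for 1 to 10 locations. These figures rest on an observer who knows or infers the block size and tracks the pile, and on an even spread over strata. The article neither states nor excludes such an observer. Existing safeguards reduce the risk without closing it.

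The medication factor is a wording gap: the likely intention can be inferred, but it is not stated, which leaves room for inconsistent or discretionary classification. Its effect cannot be sized, because the number of unmedicated patients is unknown. Selection bias is therefore possible and cheaply made less likely; it is not demonstrated.

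**What to change.** 1. **Block sizes.** For blocks not yet started, generate lists with randomly varied sizes that are small multiples of three, for example 3, 6 and 9, and do not disclose the sizes to staff who recruit or allocate. The mixing and the secrecy matter: a constant block of three would be worse than six, with one allocation in three certain. The cost is new lists and envelopes, and possibly slightly more imbalance in arm sizes from incomplete blocks.
2. **Medication factor.** Define it so that every eligible patient has exactly one level, for example: on antidepressant or mood stabilizing medication for longer than 8 weeks, yes or no. State that this and psychotherapy status are established and recorded before the envelope is drawn. The cost is a sentence or two in the Randomization section. This change is needed even if the first is declined, because varying the block size does not settle which pile an unmedicated patient belongs to.

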#### Intervention period

The ESM measurements consist of brief questionnaires on the smartphone via a link to a secured website for routine outcome monitoring (RoQua, https://www.roqua.nl). Participants who do not have a smartphone of their own will be provided with one for use during the intervention period. Participants will be instructed how to fill out the ESM measurements using their smartphone and how to interpret the questions. Participants will fill out ESM measurements five times a day during the course of their daily lives for 28 days. The measurements will occur at set points in time during waking hours (i.e., every three hours during the day, Fig. 2), which will be programmed to optimally fit the participant’s usual daily rhythm.

**Fig. 2 Fig2:**

Example of sampling times for the self-report assessments. The total sampling period covers 28 days

Participants will be asked to complete their reports preferably immediately after they receive a text message with the link to the questionnaires. To minimize memory distortion, the link expires after 30 min. Participants will be sent a reminder text message after 15 min if they did not complete the measurement yet. During the ESM period, the registration of the questionnaires is regularly checked in RoQua. In case of > 10 subsequent missing measurements, participants will receive a telephone call to ask whether they want to stop the ESM measurements. Technical support will be available throughout the study.

For both ESM modules, each measurement starts with questions about the participants’ current mood (PA, NA) and physical state, followed by questions regarding activities for the Do-module and hassles/uplifts and positive/negative thoughts for the Think-module. In addition, the morning measurements include a question about sleep, and the evening measurements a few general questions on how participants experienced the past day and how they feel about the next day. The self-assessments will be rated on dichotomous scales (e.g., for the presence of hassles/uplifts) and visual analogue scales (usually ranging from not at all (0) to very much (100)). The items for the momentary questionnaires are presented in Additional file 1: Table S1.

Participants in the intervention groups receive personalized feedback after each intervention week based on the ESM measurements. This sums up to a total of 4 feedback moments. After weeks 1–3, feedback will be e-mailed to the participant in a digital report comprising text and simple graphs (e.g., pie charts, bar graphs). After week 4, a final feedback report will be e-mailed, in which participants will also receive feedback on temporal relationships between sets of variables (e.g., PA and physical activity (Do-module), or NA and rumination (Think-module)). To this end, time-series analysis will be employed on the individual time series at the end of the ESM period. Specifically, vector autoregression (VAR) models will be applied, which are particularly suited for the investigation of the temporal dynamics between two variables [29, 30].

For both ESM modules, the feedback reports will contain increasingly rich information across the intervention period by showing participants’ changes in affective responses in daily life situations from week to week. This way, the participants could become more aware of small improvements and get increased control over influences on their mood. In the Do-module, the feedback will also show changes in activities since the start of the study and ultimately provide information on the relationship between affective responses in daily life and activities in order to refocus and redirect the participants towards occasions for emotional strength. In the Think-module, the feedback will not only show participants’ changes in mood, but also negative and positive thinking patterns across the intervention period. The final report of the Think-module will provide information on the relationship between affective responses in daily life and thinking patterns such as rumination in order to make participants aware of potential negative spirals.

A research assistant will discuss the final feedback report with the participant during a debriefing session, which takes place at the mental health care organization shortly after the end of the intervention period. The research assistant will answer questions and help participants provide meaning to the graphs according to a standardized protocol. Personal notes will be made on the printed feedback report, which the participant will take home. Feedback reports are not sent to the (future) therapist by the researcher; participants can choose for themselves whether or not they want to share this information. After discussing the feedback report, participants fill out an evaluation questionnaire on the ESM intervention and the regular questionnaires (control participants fill out the latter at home). At a later point, the intervention tool will also be evaluated through an additional semi-structured interview in a subset of participants. Participants are provided with an information letter about this interview at the end of the debriefing session.

